##### ERP Components

The changes in the ERP components throughout the training will be analyzed. For this purpose, epochs from 150 milliseconds to 550 milliseconds poststimulus onset will be extracted from the EEG data for both target and nontarget trials. Subsequently, the total power across the same centroparietal electrodes as used in [17] (ie, C3, Cz, C4, P3, Pz, and P4) will be calculated for each epoch.

The average total power for all epochs of the calibration and evaluation phases, the training phase, and the after-training phase, respectively, will be calculated. A training-to-calibration ratio of the average power for both target and nontarget trials will be obtained by dividing the average total power during the training phase by the average total power during the calibration and evaluation phases. The same will be done with the average total power during the after-training phase to obtain an after-training-to-calibration ratio.

A ratio of greater than unity indicates an increase in average total power, whereas a ratio of less than unity indicates a decrease in average total power compared to the calibration and evaluation phase. For target trials, an increase in power means that the participant improved their attention, and a decrease in power of nontarget trials can be interpreted as the participant being less distracted by nontarget flashes [17].

Appropriate statistical tests, such as ANOVA, will be conducted to analyze within-group and between-group differences in the aforementioned ratios.

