One example of a novel EEG-NFB is the adaptive P300 speller for attention training by Arvaneh et al [17]. The P300 speller was first introduced by Farwell and Donchin [18] in 1988 as a tool for patients who could not communicate, such as in the case of patients who have “locked-in” syndrome. In the speller, a matrix of symbols (eg, letters and numbers) is presented to the user. Each row and column in the matrix of symbols is highlighted or flashed in random order. When the user only focuses on the flashes of a target symbol and ignores the other flashes, the BCI can select this target symbol by identifying the row and column that elicited a P300 wave, thus allowing the user to spell words with their mind. In this process, each row and column are flashed several times, so that the signal-to-noise ratio (SNR) of the EEG signals can be increased by averaging. Usually, this number of flashes per row and column is fixed to allow the user to spell words sufficiently well in an acceptable amount of time. However, Arvaneh et al [17] progressively reduced the number of flashes in a training session based on the user’s performance to intentionally decrease the SNR. This makes it more difficult for the user to spell words correctly, thus encouraging them to improve their focus in order to maintain their performance. The researchers demonstrated that a single training session on healthy adults resulted in an increase in performance in a cognitive task, as well as an enhancement of event-related potentials (ERPs) [17].

This study intends to replicate the experiment by Arvaneh et al [17], comparing their adaptation of the number of flashes to a novel adaptation approach based on iterative learning control (ILC).

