### EEG Data Acquisition

Participants’ EEG data will be recorded during the P300 speller training phase of the experiment. EEG data will be collected using the battery-operated ANT Neuro eego rt [27] with a 32-channel waveguard cap [28]. The sintered silver–silver chloride electrodes are located in standard 10-20 positions. Impedances will be maintained below 5 kΩ during recording.

The EEG signals will be acquired in the OpenViBE software [29] at a sampling rate of 500 Hz. All channels will be band-pass filtered (1-20 Hz) and down-sampled by a factor of 4 before further processing.

Offline analysis of the EEG data will be carried out in MATLAB [30] using the EEGLAB toolbox [31]. Since this study is a replication of Arvaneh et al’s [17] study, the following offline analysis steps closely follow the steps described in the study. The continuous EEG signals will be rereferenced to Fz, band-pass filtered between 0.5 and 35 Hz and separated into baseline-corrected epochs of 150 milliseconds before the stimulus to 550 milliseconds post stimulus, where the 150 milliseconds prestimulus period is used as the baseline. Epochs with an amplitude of more than 75 µV or those with a voltage step of more than 150 µV within a 200-millisecond window will be excluded from analysis.

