#### P300 Speller Task

##### Overview

In this study, the P300 speller implementation in OpenViBE [29] is used. This P300 speller uses the xDAWN algorithm [35] to train a spatial filter that enhances the SNR of the P300 ERPs. This reduces the 32 EEG channels to 3 components, which are weighted combinations of all channels. A linear discriminant analysis classifier is used to distinguish target and nontarget trials. It should be noted that the row and column with the highest probability of belonging to the target class are chosen, even if that is below 50%. Both the spatial filter and classifier are trained for each participant using calibration data.

Figure 2 shows the 6 by 6 grid of letters and numbers that is displayed on the screen. The word to be copy-spelled and the identified symbols can be seen below the grid. If the identified symbol is the same as the target symbol, it will be displayed in green. If the identified symbol is in the same row or column as the target symbol, it will be displayed in orange and if it is wrong, it will be displayed in red.

Outside of the training phase, 12 flashes per row and column are used. Each flash lasts 55 milliseconds with an interflash interval of 117 milliseconds. Each target symbol is highlighted in blue for 6 seconds before the flashing begins.

In each run after the calibration phase, the spelling accuracy, that is, the fraction of symbols that were identified correctly, is calculated for all numbers of flashes between 1 and the actual number of flashes used.

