##### Time-Frequency Analysis

Similarly, to the training-to-calibration and after-training-to-calibration ratios of the average total power, these ratios will be calculated for the power of the alpha rhythm (7-12 Hz) of nontarget trials that are not presented immediately after a target trial. The alpha power will be calculated for the same centroparietal electrodes as before, for a period of 150 milliseconds poststimulus.

The training-to-calibration alpha ratio is the average alpha power during the training phase divided by the average alpha power during the calibration and evaluation stages, and the after-training-to-calibration alpha ratio is the average alpha power during the after-training phase divided by the average alpha power during the calibration and evaluation stages. A ratio of less than unity means that a participant is less distracted by nontarget stimuli compared to the calibration and evaluation phases [17].

Between-group differences of the training-to-calibration and after-training-to-calibration alpha ratios will be analyzed using statistical tests, such as 1-way ANOVA.

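### Nontarget total power is taken from epochs that overlap neighbouring target responses, so a change in the target P300 biases the ratio that the plan reads as distraction

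*Protocol article*

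**What the plan says.** In the protocol article, under ERP Components, "epochs from 150 milliseconds to 550 milliseconds poststimulus onset will be extracted from the EEG data for both target and nontarget trials". Power is summed over six centroparietal electrodes for each epoch and then averaged by phase. The denominator of both ratios is "The average total power for all epochs of the calibration and evaluation phases". No nontarget epoch is left out because a target is near it. The section reads a target ratio above 1 as better attention, and for nontargets says that "a decrease in power of nontarget trials can be interpreted as the participant being less distracted by nontarget flashes".

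The timing comes from the P300 Speller Task overview: "Each flash lasts 55 milliseconds with an interflash interval of 117 milliseconds". The Neurofeedback Training section describes the flash order: "Each row and column in the matrix of symbols is highlighted or flashed in random order". EEG Data Acquisition makes the epochs baseline-corrected, "where the 150 milliseconds prestimulus period is used as the baseline".

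The Time-Frequency Analysis section does restrict its epochs. Alpha power is taken from "nontarget trials that are not presented immediately after a target trial". That restriction is stated for alpha power only, where the window is 150 ms; the total-power window is 400 ms.

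**The concern.** A 400 ms window cannot isolate one flash when the next begins 117 or 172 ms later. A nontarget epoch therefore mixes the response to its own flash with the responses to neighbouring targets. Some of those target responses also fall in the 150 ms baseline that is subtracted.

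A ratio of phases would cancel this if the contaminating signal were constant. It is not: it is the target P300, which training is expected to enlarge. The nontarget ratio then rises when the target response rises, even if the participant reacts to nontargets exactly as before. It falls when the target response weakens, for example through fatigue, and the plan would read that as less distraction. The two ERP conclusions, on attention and on distraction, are thus mechanically linked. The same ratios enter the within-group and between-group tests and the correlations with random dot motion performance.

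**Working it through.** The plan gives no figure for overlap or for the expected ratio, so there is none to reproduce.

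**Inputs from the protocol.** The speller is a 6 by 6 grid, so one repetition has 12 flashes, 2 target and 10 nontarget, in random order. The flash lasts 55 ms and the interflash interval is 117 ms. If 117 ms is the gap, onsets are 55 + 117 = 172 ms apart; if it runs onset to onset, 117 ms. The protocol does not say which, so both are shown. The power window is 150-550 ms and the baseline is the 150 ms before the flash.

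**Assumed inputs, not in the protocol.** Gaussian target P300, peak 340-420 ms, SD 65 ms, amplitude 5-8 µV; background power 50-120 µV²; nontarget response zero and unchanged.

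**Step 1, where target peaks fall.** A target k flashes earlier peaks at (340 to 420) − k × interval, relative to the nontarget onset.

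| Target position | 172 ms onsets | 117 ms onsets |
|---|---|---|
| 1 earlier | 168 to 248 ms | 223 to 303 ms |
| 2 earlier | −4 to 76 ms | 106 to 186 ms |
| 3 earlier | −176 to −96 ms | −11 to 69 ms |
| 4 earlier | −348 to −268 ms | −128 to −48 ms |
| 1 later | 512 to 592 ms | 457 to 537 ms |

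A nontarget directly after a target shares 400 − 172 = 228 ms or 400 − 117 = 283 ms of its window with that target's own window. At 172 ms, targets two or three flashes earlier reach the baseline; at 117 ms, so do targets four earlier.

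**Step 2, how often.** In simulated sequences, 18% of nontargets have a target on the flash before, 18% on the flash after, and 34% one or the other. A target lies among the previous three flashes or on the next one for 60%.

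**Step 3, how much target signal nontarget epochs carry.** Mean evoked power of all nontarget epochs divided by that of target epochs:

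| | 172 ms | 117 ms |
|---|---|---|
| With baseline correction | 46-50% | about 65% |
| Without | 19-22% | up to 33% |

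A second model (peak 350 ms, SD 60 ms) gave 23-61% over the same settings.

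**Step 4, effect on the ratio.** Ratio = (1.2² × P × A² + background) / (P × A² + background), where P is evoked power at unit amplitude and A is P300 amplitude. At 172 ms with baseline correction, P is 0.312-0.323 for targets and 0.141-0.161 for nontargets.
- Weak case (5 µV, 120 µV²), nontarget: 0.141 × 25 = 3.53; (5.08 + 120)/(3.53 + 120) = 1.013. Target: 0.312 × 25 = 7.80; (11.23 + 120)/(7.80 + 120) = 1.027.
- Strong case (8 µV, 50 µV²), nontarget: 0.161 × 64 = 10.30; (14.84 + 50)/(10.30 + 50) = 1.075. Target: 0.323 × 64 = 20.67; (29.77 + 50)/(20.67 + 50) = 1.129.

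The second model, run at both intervals with 5 µV and background SD 5-10 µV, gave nontarget ratios of 1.01-1.08. These are scenarios and not a ceiling. With the 65% share at 117 ms and target power taken as 0.32, the strong case gives 0.65 × 0.32 × 64 = 13.3 and (19.2 + 50)/(13.3 + 50) = 1.09.

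**Step 5, a true fall in the nontarget response together with a 20% target gain** (second model, no baseline correction). Halving a 1 µV nontarget response gave ratios of 0.72-0.99 alone and 0.99-1.08 with the gain: hidden or reversed. Removing a 1 µV response, or halving a 1.5 µV one, gave 0.57-0.99 alone and 0.80-1.00 with the gain: weakened only. With baseline correction this model gave ratios above 1 in every such scenario, even without a target gain.

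**Step 6, what exclusion achieves** (first model, with baseline correction). Applying only the alpha-analysis exclusion at 172 ms still leaves 37-41% of target evoked power. Dropping nontargets with a target among the three preceding flashes or on the next one leaves about 0% at 172 ms and keeps 40% of nontargets. At 117 ms the same rule leaves 35-60%, because a target four flashes earlier sits in the baseline and, for early peaks, one two flashes later enters the window.

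**The case against.** The strongest reply is that the plan deliberately repeats an earlier study's offline steps, and cites that study for this interpretation. Comparability is a good reason to keep the all-nontarget ratio. It does not make the distraction reading sound, and a second ratio can stand beside the first.

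The bias from successful training also runs against the predicted fall. A reader might infer that a real training gain could manufacture a false finding of less distraction; by this route it cannot. The opposite error needs the target response to shrink, which the target ratio in the same section would tend to show.

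A reader might also infer that the predicted decrease will be hidden or reversed. The calculations do not support that: in some scenarios a true fall is only weakened and stays below 1. The size depends on P300 amplitude, latency, width, background EEG and baseline handling. The protocol fixes only the baseline, and without that correction the 172 ms share drops to 19-22%.

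Nor do the documents show that the group comparison fails. Flash timing is the same in all arms, and the Objectives section expects similar cognitive gains; if target gains are similar, the bias largely cancels between arms. Training length, spelling accuracy and the random dot motion outcomes themselves are untouched.

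These points limit size and reach. They do not remove the overlap or its direction.

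**Conclusion.** The concern holds as a bias in one stated interpretation. The overlap follows from the protocol's own timing, and nothing in the ERP Components section removes it. With an unchanged nontarget response, a larger target response raises the nontarget ratio and a smaller one lowers it. The ratio is therefore not a clean measure of distraction.

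In the scenarios run, a 20% target gain produced a spurious rise of about 1-8%. At 172 ms with baseline correction that is roughly half the accompanying rise in the target ratio, since background EEG dilutes both. The bias is thus small in absolute terms but not relative to the effect sought. These sizes rest on the assumed P300 shape, amplitude and background; the existence and direction of the bias do not rest on their exact values. The point bears on the reading of the ERP result and its correlations, not on the comparison of training length.

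**What to change.** In ERP Components, state the flash onset-to-onset interval. Base the distraction reading on nontarget total-power ratios free of target overlap, and report the all-nontarget ratio beside them for comparability with the replicated study.

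- If onsets are 172 ms apart, use nontargets with no target among the three preceding flashes and none on the next flash.
- If onsets are 117 ms apart, that rule is not enough with baseline correction. Use an overlap-correcting (deconvolution) estimate, or a wider exclusion that keeps only about 10% of nontargets.

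No new data are needed, only epoch selection or an added estimation step in the offline analysis. The cost is precision. Calibration plus evaluation has 11 letters (3 + 5 + 3) × 12 × 10 = 1320 nontarget epochs and the posttraining run has 5 × 12 × 10 = 600, before artefact rejection and without a second evaluation word. Keeping 40% leaves about 528 and 240; keeping 10% leaves about 132 and 60, which favours deconvolution at the shorter interval.

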##### Time-Frequency Analysis

Similarly, to the training-to-calibration and after-training-to-calibration ratios of the average total power, these ratios will be calculated for the power of the alpha rhythm (7-12 Hz) of nontarget trials that are not presented immediately after a target trial. The alpha power will be calculated for the same centroparietal electrodes as before, for a period of 150 milliseconds poststimulus.

The training-to-calibration alpha ratio is the average alpha power during the training phase divided by the average alpha power during the calibration and evaluation stages, and the after-training-to-calibration alpha ratio is the average alpha power during the after-training phase divided by the average alpha power during the calibration and evaluation stages. A ratio of less than unity means that a participant is less distracted by nontarget stimuli compared to the calibration and evaluation phases [17].

Between-group differences of the training-to-calibration and after-training-to-calibration alpha ratios will be analyzed using statistical tests, such as 1-way ANOVA.

##### Correlation Between EEG and RDM Performance

The potential correlation between the brain activity during the P300 speller phase of the training session and the performance in the RDM task will be investigated with tests, such as the Pearson correlation coefficient or the nonparametric Spearman correlation test. The training-to-calibration and after-training-to-calibration ratios of total power and alpha power will be used as performance metrics during the P300 speller task. Similar ratios will be obtained for the response times and accuracies of the RDM task by dividing the posttraining phase response times and accuracies by the pretraining phase response times and accuracies, respectively.

## Results

This study was approved by the Maynooth University Ethics Committee (BSRESC-2022-2474456) and is registered on ClinicalTrials.gov (NCT05576649). Participant recruitment and data collection began in October 2022. We expect to publish the results in 2023. This study is replicating the experimental protocol of Arvaneh et al [17], comparing their task difficulty adaptation approach to a novel approach using an iterative learning controller, as well as random task difficulty levels in each run.

Arvaneh et al [17] showed a significant enhancement of ERP components and performance in the RDM task after the P300 speller training, suggesting that participants’ attention improved. We expect such an improvement for all groups in this study, with changes in the length of the training between groups due to the different adaptation approaches.

## Discussion

### Overview

This study aims to evaluate the use of an adaptive P300 speller as a neurofeedback training tool for attention training. We aim to accelerate the training process using ILC and compare personalized and nonpersonalized task difficulty adaptation approaches. By replicating the experimental protocol of Arvaneh et al [17], who demonstrated the adaptive P300 speller’s potential as an easy-to-use and effective neurofeedback training tool, we seek to gather further evidence supporting this application for attention training.

The findings of this study will contribute to the understanding of how different adaptation approaches, both personalized and nonpersonalized, can impact the efficacy of neurofeedback training tools. These insights can guide the design of future BCI-based cognitive training and rehabilitation interventions. Accelerating the training with the P300 speller, without affecting its effectiveness or the users’ frustration levels, will make it a more attractive training option for people with cognitive deficits.

### Limitations

There are limitations to this protocol. The participants will only receive a single session of the neurofeedback training and therefore the long-term impacts of the neurofeedback training will not be obtained. Due to the short length of the training session, participants may not experience significant cognitive enhancements. The participants for this study will be healthy, and most likely young (due to recruitment in the university community) adults. It can be assumed that these individuals possess close to maximal cognitive abilities, which further limits the significance of the cognitive enhancements of the training.

### Conclusions

Due to an aging and growing population, the number of people with cognitive deficits and illnesses is rising. It is therefore important to develop cognitive training and rehabilitation tools that are affordable, easy to use, and effective. The adaptive P300 speller that will be evaluated in this study might have the potential to be an efficient training tool. Positive findings of this study may demonstrate that the adaptive P300 speller, and more broadly BCIs, can be effective tools in cognitive training and rehabilitation.

## Abbreviations

ADHD: attention-deficit/hyperactivity disorder
BCI: brain-computer interface
EEG: electroencephalography
EEG-NFB: electroencephalographic neurofeedback
ERP: event-related potential
ILC: iterative learning control
RDM: random dot motion
SNR: signal-to-noise ratio
